# Tailored Versus Generic Knowledge Brokering to Integrate Mood Management Into Smoking Cessation Interventions in Primary Care Settings: Protocol for a Cluster Randomized Controlled Trial

**DOI:** 10.2196/resprot.9715

**Published:** 2018-04-27

**Keywords:** tobacco, depression, health care practitioner, primary health care, knowledge broker, clinical decision support system, screening, brief intervention, integrated care pathways

## Abstract

**Background:**

Both tobacco smoking and depression are major public health problems associated with high morbidity and mortality. In addition, individuals with depression are almost twice as likely to smoke and less likely to achieve smoking cessation. In the Smoking Treatment for Ontario Patients program, an established smoking cessation program in Ontario, Canada, 38% of smokers in primary care settings have current or past depression with 6-month quit rates that are significantly lower than those without depression (33% versus 40%, *P*<.001). Integrating self-help mood management (eg, relaxation exercises and mood monitoring) with smoking cessation treatment increases long-term quit rates by 12%-20%. However, integration in real-world settings has not been reported. It is unclear which knowledge translation strategy would be more effective for motivating clinicians to provide resources on mood management to eligible patients.

**Objective:**

The objectives of this study are to investigate the following comparisons among depressed smokers enrolled in a smoking cessation program: 1) the effectiveness of generalized, exclusively email-based prompts versus a personalized knowledge broker in implementing mood management interventions; 2) the effectiveness of the two knowledge translation strategies on smoking quit rates; and 3) the incremental costs of the two knowledge translation strategies on the implementation of mood management interventions.

**Methods:**

The study design is a cluster randomized controlled trial of Family Health Teams participating in the Smoking Treatment for Ontario Patients program. Family Health Teams will be randomly allocated 1:1 to receive either generalized messages (related to depression and smoking) exclusively via email (group A) or be assigned a knowledge broker who provides personalized support through phone- and email-based check-ins (group B). The primary outcome, measured at the site level, is the proportion of eligible baseline visits that result in the provision of the mood management intervention to eligible patients.

**Results:**

Recruitment for the primary outcome of this study will be completed in 2018/2019. Results will be reported in 2019/2020.

**Conclusions:**

This study will address the knowledge gap in the implementation strategies (ie, email-based prompts versus a knowledge broker) of mood management interventions for smokers with depression in primary care settings.

**Trial Registration:**

ClinicalTrials.gov NCT03130998; https://clinicaltrials.gov/ct2/show/NCT03130998 (Archived on WebCite at www.webcitation.org/6ylyS6RTe)

## Introduction

### Background

Both tobacco smoking and depression are major public health problems with high morbidity and mortality [1-4]. Individuals with depression are almost twice as likely to be smokers [5-7], have lower long-term smoking abstinence (odds ratio [OR] 0.81, 95% CI 0.67-0.97) [1], and experience greater addiction severity and negative mood when quitting smoking [8-11].

Self-help mood management (eg, relaxation exercises and mood monitoring) integrated with smoking cessation treatment increases long-term quit rates by 12%-20% [3,4,12-15]. However, it remains unclear what knowledge translation (KT) strategy would be most effective in engaging practitioners to implement a mood management integrated care pathway (ICP) into primary care settings [16-20]. Two strategies that are commonly used in Canada to promote evidence-based practices include email communications and knowledge brokers (KBs) [17]. Emails provide targeted messages that connect relevant research evidence to specific practitioners, while KBs work one-on-one with practitioners to facilitate the implementation of an evidence-informed intervention [21] Several studies have shown that context where the intervention is being implemented is essential to take into account, in deciding which KT strategy to use [16,17]. Unfortunately, it is not known which of these KT strategies would be the most effective among Family Health Teams (FHTs) in Ontario, Canada. In Ontario, FHTs are primary health care organizations that include a team of family physicians, nurse practitioners, registered nurses, social workers, dietitians, and other professionals who work together to provide primary health care for their community [21].

### Objective

This study aims to assess whether email updates versus a KB (who will communicate with health care providers on an as-needed basis) is more effective at enabling practitioners within FHTs to provide their patients with mood management resources when needed. In addition, it will explore which of these KT strategies has the greatest effect on smoking abstinence and depressive symptoms at time of follow-up. We will also examine the incremental cost effectiveness of the two KT strategies, the proportion of eligible smokers who report using the resources, smoking cessation outcomes compared to patients without depressive symptoms, and practitioner improvement in knowledge, attitudes, skills, and satisfaction in addressing depressive symptoms in smokers.

In this paper, we describe the protocol for a cluster randomized trial. This design was chosen because the intervention cannot be delivered to individual practitioners within a clinic without substantial risk of contamination across study arms. The trial will be operationalized through the Smoking Treatment for Ontario Patients (STOP) program, an established smoking cessation program in Ontario, Canada. The STOP program offers up to 26 weeks of smoking cessation treatment, consisting of nicotine replacement therapy and behavioral counseling, at no cost to the patient.

## Methods

### Inclusion Criteria

#### Site Level

Family Health Teams (FHTs) in Ontario, Canada implementing an existing smoking cessation program (ie, the STOP program) and using the STOP’s online portal at the time of the study are eligible to participate. All FHTs operational in the STOP program as of November 2017 (n=153) will be eligible for randomization, except for those that do not use the online program portal at the time of patient enrollment (n=25). We anticipate that 128 FHTs will be randomized into the trial.

#### Patient Level

In order for a participant to be eligible for the trial, their baseline enrollment survey must be administered by the health care provider, in English, into the online portal in real time, so that the clinical interaction can be supported by the STOP portal. Therefore, those patients who are administered the baseline survey on paper, or in French, will be excluded. Patients, at the time of enrollment, must have depression (determined by a Patient Health Questionnaire [PHQ-9] score>9) or report a past diagnosis of depression.

### Pre-Implementation

To understand the needs of the FHTs and the importance of treating depression in the smoking cessation program, we developed a survey which measures organizational readiness and the extent to which an organization is willing and able to implement a specific intervention [22]. The survey consists of 12 questions addressing the six components of The National Implementation Research Network’s Hexagon Tool (ie, need, fit, resources, evidence, readiness, and capacity) [23], as well as the three readiness components described by Scaccia et al [24] (ie, motivation, general capacities, and specific capacities) [24]. Based on answers to this survey, organizations were grouped into two categories: most ready (n=44), and least ready (n=40). Organizations that did not answer the questionnaire (n=41) will be grouped together in a group labeled “unknown readiness.” The detailed answers from this survey will be useful for developing a KT strategy that will allow the project team to make informed decisions about their approach to change management.

In order to increase practitioners’ competencies to deliver a brief mood management, two interactive webinars will be presented to communicate best practices for integrating evidence-based mood interventions into smoking cessation programming. The webinar audience will include the STOP Community of Practice (n=300) consisting of implementers, physicians, and executive directors, who interact through bi-weekly teleconferences to communicate updates, clarify procedures, address barriers or gaps in program delivery, and share experiences with other practitioners.

### Trial Design

Study clusters (ie, FHTs) will receive either generalized messages (related to depression and smoking) exclusively through email (group A) or be assigned a KB who will provide personalized support through phone- and email-based check-ins (group B).

Practitioners from group A will receive one email per month for one year. The first email will provide an electronic copy of a relevant Cochrane review [15]*,* and a short description of the new depression ICP that will be integrated into the STOP portal. Subsequent communications will be based on general needs identified throughout the study. Practitioners from group B will receive individualized support from a KB communicating through interactive technology (ie, Skype) on an as-needed basis. The KB will be certified in tobacco cessation counseling and will have completed a specialty course on tobacco addiction treatment for individuals with mental illness [25,26].

Clinics are the unit of randomization. Two stratification factors are defined: (1) organizational readiness (described previously) with three levels, and (2) clinic size with two levels, resulting in six strata. Expected clinic size will be estimated based on past STOP enrollment because the actual number of eligible trial participants clinics will enroll is not directly observable a priori. Within each readiness stratum, the two levels of clinic size were set such that expected total enrollment in the two levels would be balanced. Within each of the six combined strata, clinics were randomly allocated in a 1:1 allocation ratio to control (group A) or intervention (group B). Treatment allocation (randomization) for each clinic was determined for all operational clinics en masse. Any clinic that began implementing the STOP program after the randomization cut-off date (Nov 14, 2017) will not be eligible for participation in the trial. The random assignment of treatment to clinic was computer generated using the ralloc command of statistical computer software Stata V.14.

### Blinding

This pragmatic, cluster trial is designed to evaluate an intervention to change practitioners’ behavior. Blinding of the clinic through its practitioners will therefore not be possible as the practitioner will be aware of the presence or absence of the KB. Participating clinics will not be informed of their treatment allocation until the trial begins. Data analysis will be blinded to treatment allocation.

### Interventions

#### Patient Screening and Brief Intervention

Across all sites, practitioners will receive the same depression ICP integrated into the STOP portal. Currently, patients are asked to self-report on past diagnosis of depression and screened for current depression using the PHQ-9. The PHQ-9 is a self-completed, 9-item instrument with each item aligning with the Diagnostic and Statistical Manual of Mental Disorders (version IV)’s criteria for depression, and developed specifically for use in primary care [27,28]. As part of the new ICP, the STOP portal will identify patients screened as having current or past depression, and prompt practitioners to provide a brief intervention and refer an evidence-based package of resources [29,30] (see Figure 1). Brief intervention messaging will be designed using the Canadian Network for Mood and Anxiety Treatments guidelines [31] and tailored to patients’ depression levels based on their PHQ-9 score. Levels can range anywhere from low risk of depression, which would warrant the usual standard of care, to major depression with severe consequences [31]. If patients’ screening results indicate risk of moderate or severe depression, practitioners will be prompted to consult with a team physician to determine next steps (eg, medication adjustment or psychiatric referral). For patients who endorse suicidal ideation, the ICP will guide practitioners to conduct an additional assessment. Whenever an intervention is warranted, practitioners will be encouraged to discuss other health risk behaviors that influence patient mood, including alcohol use and stress. Figure 1 presents a visual depiction of the study work flow.

The evidence-based resource package, which practitioners will be able to print or email it to patients, will include:

Relaxation and mindfulness exercisesSelf-monitoring sheets to record each cigarette smoked, the activities they engaged in, and overall mood at the end of each day for 2 weeksProblem-solving attitudes and skills-building activities

### Outcomes

The primary outcome will be the provision of the mood management intervention to eligible patients upon completion of the STOP smoking cessation program enrollment. This dichotomous outcome will be measured as positive by a response of “Patient accepted the resource” to the practitioner question “Did the patient accept or decline the resource?”. In contrast, the outcome will be measured as negative if given a response of “Patient declined the resource” to the practitioner question “Did the patient accept or decline the resource?” or a response of “no” to the practitioner directive “Provide this patient with resources on mood management.”

The secondary outcome will be patient smoking abstinence at the 6-month follow-up survey, as measured by a negative response to the seven-day point prevalence question “Have you had a cigarette, even a puff, in the last 7 days?”. Self-reporting has been verified as a valid estimate of smoking status [32].

**Figure 1 figure1:**
[figure not shown]
Study workflow diagram.

The tertiary outcome will be a cost-effectiveness analysis (CEA), evaluating the delivery of each intervention from the health care system, and societal perspectives. The CEA will include the costs of developing, maintaining, and running each intervention in addition to costs associated with personnel, training, supplies, and services. The incremental cost-effectiveness ratio (ICER) will be the primary outcome of the CEA. An additional measure of interest will be the 95% confidence interval for the ICER, which will be estimated using nonparametric bootstrap resampling techniques [33-36]. This method is commonly used when undertaking economic evaluations alongside clinical trials [37,38].

Other outcomes measured in this study will include change in PHQ-9 score between the baseline and 6-month follow-up surveys, the proportion of eligible smokers who report using the materials, smoking cessation outcomes compared to patients without depression, and practitioner improvement in knowledge, attitudes, skills, and satisfaction in addressing depression in smokers.

### Covariates

Patient characteristics known to affect quit outcomes include age, gender, socioeconomic status, having a quit date, alcohol and other substance use, other mental health diagnosis and the Heaviness of Smoking Index [39]. Site and patient level covariates will be treated as potential confounders in the statistical analyses.

### Sample Size

A sample size of 1224 patients per group (2446 total) was estimated using a method that accounts for intracluster correlation (ICC) within each FHT and uneven cluster sizes [40]. Using past STOP enrollment as a data source, we estimated an ICC of ρ=.032, cluster size variation coefficient of 1.24, an average annual enrolment of 24 patients, the proportion of control group patients who are provided the mood management intervention (p1) to be 0.08, and set alpha=.05 and power=.80. The minimum desired effect size was set at a risk difference=0.06. Based on enrollment in 2016-2017, we estimate the required sample size for the primary outcome will be achieved in less than 12 months.

### Statistical Analysis

All analyses will adopt an intention-to-treat principle in which sites and patients will be analyzed in the trial arm to which they are randomized. Cluster specific methods will be used because the practices, rather than patients, will be randomized, and variance in how patients are managed, and in patient quit outcomes, will be partly explained by the practice.

#### Primary and Secondary Outcomes

The association between the KT intervention and the primary outcome (ie, delivery of mood management interventions) will be analyzed using a generalized estimating equation (GEE) fitted for logistic regression, using a population-averaged method. Stratification variables will be included as covariates. An exchangeable correlation matrix and robust standard errors will be specified. All outcomes are recoded by the STOP portal system and thus a full case analysis will be used.

The association between KT intervention and the secondary outcome (ie, smoking abstinence at 6-month follow-up) will be analyzed using a GEE as described above. All patients are invited to complete the 6-month follow-up survey, but not all do, so missing outcome data are expected. Therefore, we will conduct a single imputation of the best-case scenario (all patients not smoking) and a single imputation of the worst-case scenario (all patients smoking). If the analyses from the two case scenarios imply different conclusions, multiple imputations will be performed accounting for the clustered structure of the data. All study analyses will be performed in Stata 14 [41].

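### The abstinence GEE names only the stratification factors as covariates; prespecifying each FHT's pre-trial quit rate would be a cheap, modest and optional gain in precision

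*Protocol article*

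**What the plan says.** In Primary and Secondary Outcomes, the primary outcome is analysed by a population-averaged logistic GEE with exchangeable correlation and robust standard errors, and "Stratification variables will be included as covariates". Smoking abstinence at 6 months "will be analyzed using a GEE as described above". Trial Design gives the stratification factors as "1) organizational readiness (described previously) with three levels, and (2) clinic size with two levels, resulting in six strata".

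The Covariates section adds that "Site and patient level covariates will be treated as potential confounders in the statistical analyses". It lists patient characteristics related to quitting, but no site covariate and no earlier clinic-level outcome.

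Three other places bear on the point:
- Statistical Analysis accepts that "variance in how patients are managed, and in patient quit outcomes, will be partly explained by the practice".
- The abstract's Background reports, for STOP primary care smokers with current or past depression, "6-month quit rates that are significantly lower than those without depression" (33% versus 40%).
- Sample Size obtains its planning values "Using past STOP enrollment as a data source", and Trial Design sets the size strata from each clinic's past enrollment.

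**The concern.** A clinic's own earlier level of an outcome is often the best available predictor of its level during a trial. Readiness and a two-level size factor do not measure it. STOP has already followed past enrollees to 6 months and knows their depression status, so the abstinence model leaves unused a covariate that was probably available before randomisation.

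What is at stake is precision only. Differences between FHTs that a past quit rate could explain stay in the standard error of the arm comparison. This is most relevant to abstinence, because the Discussion itself concedes that a change in abstinence may be underpowered for the cost-effectiveness ratio.

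**Working it through.** **1. The plan's own sample size.** Inputs from Sample Size: p1 = 0.08, risk difference 0.06 (so p2 = 0.14), alpha .05 (taken as two-sided), power .80, ICC .032, mean size 24, CV 1.24.
- Unclustered n per group = (1.960 + 0.842)² × (0.08×0.92 + 0.14×0.86) / 0.06² = 422.97.
- Design effect with 51 clusters per arm (1224/24) = 1 + ((1.24² × 50/51 + 1) × 24 − 1) × .032 = 2.894.
- 422.97 × 2.894 = 1224, the stated figure. It carries the full unadjusted ICC, so the planned size does not depend on any further covariate.

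**2. How much variance lies between FHTs (primary-outcome inputs).** The size-weighted design effect gives (2.894 − 0.968)/2.894 = 67%. The specified exchangeable GEE, however, down-weights large FHTs. With lognormal sizes (mean 24, CV 1.24) its design effect, mean(m) / mean[m/(1 + (m−1)×.032)], is about 2.15. The between-FHT share is then 46% of the weighted variance, or 1 − 0.968/2.15 = 55% counted as above: roughly half.

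**3. Gain for abstinence.** Assumptions, none of them in the documents: ICC .01 or .03; 60% follow-up; two past years; r = correlation between an FHT's true past and true trial effect, 0.5 to 0.9. The enrollment mean and CV are taken from Sample Size. Trial responders per FHT: 24 × 0.6 = 14.4. Past responders: 28.8.

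Reliability of the past rate = n×ICC / (1 + (n−1)×ICC):
- ICC .01: 0.288/1.278 = .225
- ICC .03: 0.864/1.834 = .471

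The shrunken past rate explains a share r² × reliability of the between-FHT variance. Hand example at ICC .03, r = 0.7:
- Share explained: 0.49 × .471 = .231.
- Design effect before: 1 + ((1.24² + 1) × 14.4 − 1) × .03 = 2.066.
- Design effect after: 0.97 + 36.54 × .03 × (1 − .231) = 1.813.
- Fall in SE: 1 − √(1.813/2.066) = 6.3%.

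For the exchangeable GEE, information is proportional to the mean of m/(1 − ICC + m×τ). Here τ = ICC before adjustment and ICC × (1 − r² × reliability at that FHT's size) after it. With lognormal sizes, the fall in SE is:

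| ICC | r = 0.5 | r = 0.7 | r = 0.9 |
|---|---|---|---|
| .01 | 1.1% | 2.2% | 3.8% |
| .03 | 2.8% | 5.9% | 10.7% |

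This is a large-sample approximation on the risk scale, for patients with observed follow-up.

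**4. Is there a past rate for each outcome?**
- Abstinence: quit rates by depression status are reported for the program as a whole. Clinic-level enrollment was used for the strata. An FHT-level rate follows by reasonable inference.
- Provision of the resource: the outcome is the practitioner's portal response about the resource, and the prompting is new with the trial ("As part of the new ICP, the STOP portal will identify patients screened as having current or past depression"). Sample Size does not say what past measure stood behind p1 = 0.08 and the ICC.

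**The case against.** The strongest reply is that nothing here is wrong. An exchangeable GEE with robust standard errors, adjusted for the stratification factors, is valid, and the sample size is reached without further adjustment. The Covariates section already foresees site-level adjustment, and the choice of site covariates may be left to an analysis plan that is not shown. The gain depends on an r that nobody has reported. High values are doubtful when every FHT receives a new pathway, and half also a knowledge broker, between the two periods. All of this stands, and it limits the point to an optional improvement. What remains is that the article does fix a covariate set for the abstinence model, and no prior clinic-level outcome is named in it or anywhere else.

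A reader might also infer three stronger claims that the documents do not support:
- *That both models ignore a past rate STOP already holds.* For provision no such FHT-level record is described; at best a proxy exists.
- *That adjustment is confined to readiness and size.* The Covariates section says otherwise in general terms. Nor is unknown readiness missing data: it is a defined stratum level.
- *That two thirds of the variance is between FHTs and could be removed.* That share belongs to the size-weighted sample-size formula. Under the specified GEE it is roughly half, and a past rate removes only part of it.

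**Conclusion.** The point holds for the abstinence model as a modest, optional gain in precision: about 1-4% off the standard error at an ICC of .01 and 3-11% at .03. These figures rest on two past years of data, 60% follow-up, r between 0.5 and 0.9, and quit rates being retrievable by FHT. The last of these is likely but not stated. For the primary outcome the documents do not establish that a usable past FHT rate exists, so no gain is claimed. There is no bias, no invalid test and no fault in the stated sample size.

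**What to change.** Before analysis, and without sight of outcomes by arm, name one additional FHT-level covariate in the abstinence GEE: the FHT's pre-randomisation 6-month quit rate among STOP smokers with current or past depression.
- Shrink each rate toward the overall mean so that small FHTs do not add noise, and give FHTs without past data that mean.
- Use follow-up surveys completed before the cut-off of 14 November 2017, that is, enrollments up to about mid-May 2017.
- If multiple imputation is triggered, put the same covariate in the imputation model.

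For the primary GEE, state which past measure produced the ICC and p1. Add it as a covariate only if it is available by FHT.

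The cost is one extract of existing STOP data, one degree of freedom and a sentence of analysis text. No new patients or data collection are needed.

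### The best-case and worst-case fill-ins for missing 6-month abstinence do not bound the treatment effect, so their agreement is a poor reason to skip multiple imputation.

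*Protocol article*

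**What the plan says.** The Outcomes section of the protocol article names one secondary outcome: "The secondary outcome will be patient smoking abstinence at the 6-month follow-up survey", a binary seven-day point-prevalence measure. Under Primary and Secondary Outcomes it "will be analyzed using a GEE as described above", that is, with a logistic GEE with exchangeable correlation, robust standard errors and the stratification variables as covariates.

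The same section accepts that data will be missing: "All patients are invited to complete the 6-month follow-up survey, but not all do, so missing outcome data are expected". It then plans a "single imputation of the best-case scenario (all patients not smoking) and a single imputation of the worst-case scenario (all patients smoking"). The next step is conditional: "If the analyses from the two case scenarios imply different conclusions, multiple imputations will be performed accounting for the clustered structure of the data".

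Each scenario gives the same value to missing patients in both arms. No scenario lets missing patients differ by arm. The article states no follow-up rate, and no intracluster correlation (ICC) or power for abstinence.

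**The concern.** The labels best case and worst case describe the overall quit rate. They do not describe the comparison between arms, because the same fill-in is applied to group A and group B. Two analyses that move both arms together can agree with each other while saying little about how missing data affect the contrast. Yet agreement is the condition under which the plan stops without multiple imputation.

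At stake are the size of the effect reported for the secondary outcome and any statement that it is robust to missing data. By inference, the ICER for quit rates is also affected. The Tertiary Outcomes section does not say which abstinence data feed that ratio, but if a diluted difference went into the denominator, halving the difference would double the ICER.

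**Working it through.** **The plan's own figure.** The only sample size given is for the primary outcome, 1224 per group, from "we estimated an ICC of ρ=.032, cluster size variation coefficient of 1.24, an average annual enrolment of 24 patients", 0.08 versus 0.14, alpha 0.05 (taken as two-sided) and power 0.80.
- Unadjusted size per group: 7.849 × (0.08×0.92 + 0.14×0.86) / 0.06² = 423.0.
- Design effect: 1 + ((1 + 1.24²)×24 − 1)×0.032 = 2.917, giving 1234.
- With the factor (k−1)/k on the squared variation coefficient, and k = 1224/24 = 51 clusters per arm, the design effect is 2.894, giving 1224.

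The stated figure is reproduced. It is used below only as the number of patients per arm.

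**Algebra of the two scenarios.** Let f be the follow-up fraction and q the quit rate among responders, with subscripts A and B for the arms.
- Worst case: arm rate = f·q, so RD_worst = fB·qB − fA·qA.
- Best case: arm rate = f·q + (1 − f), so RD_best = RD_worst + (fA − fB).
- The gap RD_worst − RD_best is exactly fB − fA, whatever the non-responders did.
- If fA = fB = f, both equal f·(qB − qA), whereas a missing-at-random analysis targets qB − qA.

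**Dilution.** The control rate of 33% is the quit rate that the abstract gives for smokers with depression: "6-month quit rates that are significantly lower than those without depression (33% versus 40"%). Taking 40% for group B responders, and taking the follow-up rates below, are assumptions. The missing-at-random target is 7.0 points, OR (0.40/0.60)/(0.33/0.67) = 1.35.

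| Follow-up, both arms | RD, both scenarios | OR worst | OR best |
|---|---|---|---|
| 70% | 4.9 points | 1.29 | 1.22 |
| 50% | 3.5 points | 1.27 | 1.18 |
| 30% | 2.1 points | 1.24 | 1.15 |

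**Not a bound.** Letting missing patients differ by arm gives f·(qB − qA) ± (1 − f). With 40% missing per arm and equal responder rates, that is −40 to +40 points; the planned pair gives 0 and 0. At 50% follow-up with 33% versus 40%, it is −46.5 to +53.5 points; the planned pair gives 3.5 and 3.5.

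**What the rule does react to.** With follow-up of 50% versus 60% and 33% quitting among responders in both arms, RD_worst = 0.198 − 0.165 = +3.3 points and RD_best = 0.598 − 0.665 = −6.7 points. The gap is the 10-point difference in follow-up.

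**Behaviour under a logistic analysis.** This was simulated with 64 clusters per arm, about 1224 patients per arm, a cluster-robust log odds ratio without strata, and 2000 runs. The ICCs for abstinence, 0.01 and 0.032, are assumptions. Each pair of results is in that order.
- Equal 50% follow-up, 33% versus 40%: power with full data is 85% and 64%. Both scenarios are non-significant, so imputation is skipped, in 31% and 43% of trials. The scenarios disagree in 39% and 31%.
- Follow-up 50% versus 60%, no effect: the scenarios disagree in 98% and 95%.
- Equal 50% follow-up, responders 33% versus 45%, non-responders 45% versus 33%. Each arm's true rate is (33 + 45)/2 = 39%, so there is no effect, but both scenarios show 0.5 × 12 = 6.0 points. Both are significant for group B in 82% and 70% of trials, and imputation is not triggered.

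**The case against.** Four objections carry weight.

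1. A reader might infer that the rule detects nothing but unequal follow-up, that agreement is all but guaranteed, and that multiple imputation would never be run. The planned analysis does not support that reading. The identity is exact for the risk difference, but under a logistic GEE the odds ratios and p-values differ even when follow-up is equal. At 60% follow-up, 33% versus 39%, 1224 per arm and no clustering, the worst case gives OR 1.24 (p = 0.030) and the best case OR 1.16 (p = 0.067), which would trigger imputation. Chance imbalance in follow-up adds to this.

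2. A reader might infer that a real effect would routinely be declared absent. In the 33% versus 40% example, both scenarios are non-significant while a complete-case analysis, used as a proxy for missing at random, is significant in only about 2% to 3% of simulated trials. Most trials in which both scenarios are null would be null under the better method as well.

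3. Multiple imputation is not a cure for arm-dependent non-response. In the opposed-arms example the complete-case analysis is itself falsely significant in 97% and 89% of trials, and standard imputation would carry much the same bias. That example is deliberately extreme. It shows what the rule cannot flag, not what is likely.

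4. Dilution is measured against missing at random. If non-responders really are smoking, the worst-case analysis is not diluted. The article does not commit to that assumption, since it sets the all-abstinent scenario beside it on equal terms.

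What an imputation model would contain is a matter for the analysis plan, and its absence here is no fault. None of these points makes agreement between the two scenarios evidence of robustness, or justifies using it to decide whether imputation is run.

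**Conclusion.** The concern holds in this form: the two scenarios respond mainly to differential follow-up and do not bound the treatment effect, and their agreement switches off multiple imputation although the shared estimate may be diluted or biased. The gap identity and the shrinkage by the follow-up fraction need no assumption about the ICC. The size in points does rest on assumptions: at 30% to 70% follow-up and responder rates of 33% and 40%, the shared risk difference is 2.1 to 4.9 points against 7.0. The simulated percentages also depend on the assumed ICCs and on a simplified version of the planned model.

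The harm falls chiefly on the point estimate and on any claim of robustness, and less often on significance. A reader might extend this to the main result of the trial, but the article says that the primary outcome is recorded by the portal, and this rule is not applied to it. The point concerns the secondary outcome and, by inference, the quit-rate ICER. It is a should-fix.

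**What to change.** - Make multiple imputation that respects the clustering the prespecified analysis of 6-month abstinence, run whatever the other analyses show, and delete the condition that triggers it.
- Keep missing = smoking in both arms as one named sensitivity analysis.
- Replace the all-abstinent scenario with a tipping-point analysis in which the assumed quit rate among non-responders differs by arm. This is the part that addresses arm-dependent, non-random missingness; imputation alone does not.
- State which abstinence estimate feeds the quit-rate ICER.

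The cost is plan wording and some programming, with no new data. The headline estimate will then rest on a missing-at-random assumption, which should be stated. The article reports that recruitment was not complete at submission, so at that stage the change could still be made before 6-month results were known.
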